**8 Adverse events (AE)**

An adverse event (AE) is defined as any untoward medical occurrence in a subject administered a pharmaceutical product which not necessarily have a causal relationship with this treatment. A serious adverse event (SAE) is any AE that is fatal, is life threatening, is disabling or incapaciting, or requires in-patient hospitalisation or prolongs a current hospitalisation.

Any AE occurring during the trial must be documented in the subject’s medical record and on the AE page of the CRF, SAE on the SAE page of the CRF. For each AE recorded the following information is collected: date of onset, date of resolution, description of the event, concomitant medication, test results, and the relationship with one or more of the antiretroviral agents.

All AE that are both serious and unexpected are subject to expedited reporting by the investigator to national regulatory agencies.

If the SAE is fatal or life threatening, a preliminary reporting should be made as soon as possible, but not later than 7 calendar days after first knowledge by the investigator, followed by a complete report within 8 additional calendar days.

For all other serious and unexpected SAEs a report should be made as soon as possible, but not later than 15 calendar days after first knowledge by the investigator.

All AE and SAE should be registered in the CRF and reported to the coordinating center. All SAE should be reported to the coordinating center within the timelines stated above.

The coordinating center will put all AE together and give details in a final report.

**9 Data analysis and statistical methods**

The trial will randomise (1:1:1) 150-210 subjects in three treatment arms.

The subjects will be followed for 144 weeks. Interim analysis will be assessed when all subjects have completed 24, 48 and 96 weeks of therapy.

Both intention to treat analyses and on-treatment analyses will be performed.

The comparisons between treatment arms with respect to treatment failure will be performed by survival tests, which take the follow up periods into account. Other comparisons will be performed by chi-square test (presence of side effects) including all three treatment groups and Kruskal-Wallis test for continuous variables. The last mentioned test is a generalization of Mann-Whitney’s test applicable on three groups. Two-tailed test at the significance level 0.05 will be used.

Figure 1

N=65 in each one of two groups compared. The probability of treatment success is P1 and P2 in the two groups. From the figure we can read that if P1 is 0.70, e.g., then P2 has to exceed 0.90 for achieving the power 80%. The line y = x is given in order to facilitate the reading of the figure. The power calculation was performed for Fisher’s exact test at the level 0.05, two-tailed test, though survival tests will be used. However, the power determination for the survival test needs more specifications than available at present and the difference in power is small.

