**4 Treatment regimens**

**4.1 Randomised treatment arms**

Patients will be randomized to one of three study arms (1:1:1). Randomization will be stratified according to CD4-cell count (above or below 200 x 106/l) and plasma HIV-RNA level (above or below 100 000 copies/ml).

Study arms:

1. lopinavir/ritonavir (Kaletra®) 400/100 mg BID + 2 NRTIs BID

2. atazanavir (Reyataz ®) 300 mg QD + ritonavir (Norvir®) 100 mg QD + 2 NRTIs QD

3. efavirenz (Stocrin®) 600 mg QD + 2 NRTIs QD

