***7.1.2 Randomisation***

Patients eligible to the study and who have signed informed consent may be randomised as soon as results from viral load and CD4 cell count measurements are available.

The randomisation (1:1:1) is performed at the Department of Infectious Diseases, Sahlgrenska University Hospital/Östra and is stratified for CD4-cell count (< or ≥ 200 x 106/ml) and plasma HIV-1 RNA level (< or ≥ 100 000 copies/ml).

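### Section 9 does not carry the two randomisation strata into the treatment-failure test and names tests that use neither strata nor baseline covariates; separately, the CD4 stratum cut-off is written in two units that differ 1000-fold

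*Protocol*

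**What the plan says.** Section 4.1 sets the design: "Randomization will be stratified according to CD4-cell count (above or below 200 x 106/l) and plasma HIV-RNA level (above or below 100 000 copies/ml"). Section 7.1.2 repeats it in another unit: the randomisation "is stratified for CD4-cell count (< or ≥ 200 x 106/ml) and plasma HIV-1 RNA level (< or ≥ 100 000 copies/ml"). Section 6.1 gives the same cut-offs as 7.1.2 and adds that the screening values define the strata.

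Section 9 is the protocol's whole statistical section. For the primary endpoint: "The comparisons between treatment arms with respect to treatment failure will be performed by survival tests, which take the follow up periods into account". It names no particular survival test and mentions neither strata nor covariates. For the rest it names a three-group chi-square test for side effects and a "Kruskal-Wallis test for continuous variables". The error rate is fixed by "Two-tailed test at the significance level 0.05 will be used".

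The power statement rests on "N=65 in each one of two groups compared", and its worked example is that "if P1 is 0.70, e.g., then P2 has to exceed 0.90 for achieving the power 80" per cent. It adds: "The power calculation was performed for Fisher’s exact test at the level 0.05, two-tailed test, though survival tests will be used".

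Section 5.4 lists change from baseline in CD4 count (item 5) and in plasma lipids (item 11) as secondary endpoints. Section 7.1.1 and Table 1 show that the starting values are collected.

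**The concern.** A trial stratifies its randomisation on factors that it expects to predict outcome. Stratified allocation makes the arms more alike than chance would. A test that ignores the strata still uses a variance that allows for chance imbalance, so it overstates the uncertainty. The result is a test with true size below the nominal 5% and some loss of power. With 50-70 patients per arm, even modest precision is worth keeping.

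The same reasoning applies to CD4 and lipid changes. The baseline value is available, and a plain Kruskal-Wallis test does not adjust for it.

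The unit conflict is a different kind of problem. It concerns the definition of a stratification factor, so it affects how patients are allocated and how any stratified analysis would be coded.

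**Working it through.** **Step 1. The protocol's own power figure.** Inputs from section 9: n = 65 per group, two-sided 0.05, Fisher's exact test, P1 = 0.70. Exact power is the sum, over all pairs (i, j) of success counts with Fisher p ≤ 0.05, of Bin(i; 65, 0.70) × Bin(j; 65, P2).

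- P2 = 0.90: 77.5%
- P2 = 0.905: 80.3%

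So 80% is reached just above 0.90, as the protocol says. The sample-size statement is reproduced and is not in question.

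**Step 2. What stratification adds at that example.** The log-rank statistic sums observed minus expected failures, U = Σ(d₁ − d·n₁/n), with variance V = Σ d(n − d)/(n − 1)·(n₁/n)(1 − n₁/n), over failure times. The unstratified test uses one risk set. The stratified test forms U and V within each of the four CD4 × HIV-1 RNA strata and adds them.

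Assumptions not in the documents:
- each factor present in half the patients;
- proportional hazards, with a prognostic hazard ratio h per factor, so stratum hazards are 1 : h : h : h²;
- permuted blocks of 6 within strata.

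Failures were recorded at the protocol's visit weeks. The base hazard b in each arm solves Σ ¼·exp(−b·m_k) = S, where m_k is the stratum multiplier and S the arm's success probability. There were 4,000 two-arm and 3,000 three-arm trials per setting. The third success rate (0.80) is also assumed.

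| h per factor | Two arms, 0.70 vs 0.90: unstratified → stratified | Three arms, 0.70/0.90/0.80: unstratified → stratified |
|---|---|---|
| 1 | 83.5% → 83.4% | 73.6% → 73.6% |
| 1.5 | 83.6% → 83.7% | 75.4% → 76.0% |
| 2 | 83.9% → 85.2% | 74.9% → 77.1% |
| 3 | 85.7% → 88.2% | 76.5% → 80.3% |

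The largest gains are 88.2 − 85.7 = 2.5 points for two arms and 80.3 − 76.5 = 3.8 points for three. A second two-arm simulation (8,000 trials, near-perfect balance within strata) gave 83.5% → 84.9% at h = 2 and 84.2% → 87.8% at h = 3, gains of 1.4 and 3.6 points.

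**Step 3. Type I error, success 0.70 in every arm.**

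| h per factor | Two arms: unstratified / stratified | Three arms: unstratified / stratified |
|---|---|---|
| 1 | 4.7% / 4.7% | 5.2% / 5.1% |
| 1.5 | 5.0% / 5.3% | 5.0% / 5.0% |
| 2 | 4.8% / 5.3% | 3.8% / 4.7% |
| 3 | 3.5% / 5.7% | 3.0% / 5.6% |

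The Monte Carlo standard error at 5% is √(0.05 × 0.95/4000) ≈ 0.3 points (0.4 for 3,000 trials). The near-perfect-balance simulation gave 2.4-3.9% unstratified and 4.6-5.3% stratified.

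**Step 4. A scenario with more events.** At 0.50 vs 0.72 success, 65 per arm, 2,500 trials:
- h = 1: 75.2% → 75.3%
- h = 1.5: 73.5% → 74.6%
- h = 2: 76.3% → 79.3%
- h = 3: 77.7% → 85.8%, a gain of 8.1 points

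Size at h = 3 was 3.0% unstratified and 5.4% stratified. A separate set of 4,000 trials gave 74.3% → 77.6% at h = 2 and 77.3% → 84.5% at h = 3, with size at h = 3 of 4.0% unstratified and 5.9% stratified.

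**Step 5. The CD4 cut-off.** One litre is 1000 ml, so 200 x10^6/ml equals 200 x10^9/l, 1000 times the section 4.1 value. Section 3.1 describes treatment starting in the range 200 to 350 x10^6/l. The literal /ml cut-off is 200 x10^9 / 350 x10^6 ≈ 571 times the top of that range, so every patient would fall below it.

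**The case against.** The strongest reply is that section 9 never says the survival test is unstratified. A stratified log-rank test or an adjusted Cox model fits its wording, and this choice is commonly left to a statistical analysis plan, which is not among the documents. That stands. A reader might infer that the protocol commits to an unstratified primary test; it does not. The reply does not cover the named chi-square and Kruskal-Wallis tests, which are a stated choice, or the unit conflict.

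Four stronger readings are also unsupported:

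- **Large power loss.** The 8-point gain needs both 0.50 vs 0.72, which the protocol text does not give, and a ninefold hazard spread across strata. Section 9's definite example is 0.70 vs 0.90. The broad failure definition in section 5.5.1 makes a higher failure rate conceivable, but section 3.1 reports better results in Scandinavia than internationally.
- **Excess false positives or wrong confidence intervals.** Ignoring the strata errs on the conservative side, and section 9 mentions no intervals.
- **A known variance saving from baseline adjustment.** The ratio (1 + r)/2, which is 0.75 at r = 0.5 and 0.85 at r = 0.7, compares analysis of covariance with a parametric comparison of change scores under equal variances. It does not describe a Kruskal-Wallis test, and r is not in the documents. A Kruskal-Wallis test on change from baseline remains valid in a randomised trial.
- **No cost at all.** At 50 per arm, four equal strata hold 50/4 = 12.5 patients per arm. At 10-30% failure that is 1.25 to 3.75 events per cell, fewer if the strata are unequal.

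On the unit, section 3.1 uses x10^6/l, so the intended scale is fairly evident. There is no evidence that anyone would be randomised on the literal /ml value.

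**Conclusion.** The point holds as a modest improvement in efficiency and a clear error of unit. The planned analysis is not invalid. The strata define the randomisation but do not reappear in section 9. The primary test is unspecified in this respect, and the named secondary tests leave out strata and baseline covariates.

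At the protocol's example the gain from stratifying is nil if the factors are not prognostic, about 1 to 2 points at a hazard ratio of 2 per factor, and about 2.5 to 4 points at 3. The unstratified test's size drops to about 2.4-4% when the factors are strongly prognostic. Stratified size lay between 4.6% and 5.9% across all simulations. These figures depend on the assumed hazard ratios, equal-sized strata and proportional hazards, none of which the protocol supplies. The benefit of baseline adjustment for CD4 and lipids is real in direction, but its size cannot be derived from the documents.

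The CD4 conflict between section 4.1 and sections 6.1 and 7.1.2 needs no assumption: it is a 1000-fold discrepancy in a figure on which allocation depends.

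**What to change.** In section 9, state that treatment failure is compared with a log-rank test stratified by screening CD4 count and HIV-1 RNA at the randomisation cut-offs, or with a Cox model adjusted for those two factors. The adjusted Cox model is the natural choice if some strata turn out very small. State also that CD4 and lipid changes are analysed with adjustment for the baseline value, using a rank-based analysis of covariance if the data are skewed.

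Reconcile the CD4 cut-off so that sections 4.1, 6.1 and 7.1.2 give one unit, noting that section 3.1 uses x10^6/l. Confirm that the randomisation procedure at the coordinating department uses the same value.

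The cost is wording only, since every variable is already collected. The statistical price is the slight excess size that sparse strata can bring, up to about 5.9% in simulation. The sample size does not need to change.

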**5.2 Secondary objectives**

1. To clarify whether there are any differences in adherence to treatment between the three arms.

2. To address whether there is a difference between the arms in the incidence of side-effects, including hyperlipidemia, leading to regimen discontinuations or changes.

3. To evaluate differences between the arms in the kinetic of viral suppression during the first four weeks of treatment (optional).

4. To explore the reason for premature discontinuing of randomised treatment.

5. To determine differences in the CD4-cell count response

6. To assess the safety and tolerance of the three treatment arms

7. To assess changes in genotypic resistance in plasma HIV-1 over the study period in the different arms

8. To determine the plasma concentration of the PIs and NNRTIs in steady state, i.e. 2-4 weeks after starting study medication

9. To assess changes in laboratory parameters, plasma lipids included, over the study period

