**6 Investigational plan**

**6.1 Trial design**

This is a phase IV, randomized open-label multicentre trial on antiretroviral effect of three different treatment regimens, one standard PI/r+2NRTI BID, and two QD regimens, NNRTI+2NRTI and PI/r+2NRTI respectively, on antiretroviral naïve HIV-1 infected patients.

Antiretroviral naïve HIV-1-infected patients with indications to start antiretroviral treatment could be included in the study. If the patient is subject to start treatment and thereby could be included in the study is judged by the clinician in agreement with the patient, and in agreement with the Swedish National Guidelines. An estimation of approximately 50-70 patients in each arm are to be included during two years.

Patients will initiate treatment with one of the three study arms (see 4 Treatment Regimens)

The randomisation is performed at the Department of Infectious Diseases, Sahlgrenska University Hospital/Östra and is stratified for CD4-cell count (< or ≥ 200 x 106/ml) and plasma HIV-1 RNA level (< or ≥ 100 000 copies/ml) (see 7.1.2).

Potentially eligible subjects will attend the clinic for a screening assessment. The CD4-cell count and HIV-1 RNA level at the screening visit will be used in stratification in the randomization process. Subjects will be randomized into one of three treatment arms and followed in accordance with the study plan.

Subjects will continue to receive the randomized treatment for the duration of the trial (i.e. 36 months). The NRTI backbone is allowed to be changed due to reasons other than virological failure, mainly side effects (see 6.3).

For patients in treatment arm 1 that acquire grade 3-4 hyperlipidemia, lopinavir/ritonavir could be switched to atazanavir/ritonavir in a roll-over-protocol (see 9 Roll-over protocol).

The patient could be followed in the study also if a visit has been missed of any reason, however, the baseline visit has to be performed.

The investigational site or the patient can anytime and of any reason decide to discontinue the study.

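### The chi-square on presence of side effects ignores time on the randomised drug, so the on-treatment comparison of late or cumulative effects can flatter an arm that patients leave for unrelated reasons

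*Protocol*

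**What the plan says.** Protocol section 9 compares treatment failure by "survival tests, which take the follow up periods into account". The next sentence turns to the remaining comparisons: "Other comparisons will be performed by chi-square test (presence of side effects) including all three treatment groups". Both intention-to-treat and on-treatment analyses are planned, and planned follow-up is 144 weeks for every subject.

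Safety is a named secondary objective in section 5.2: "To assess the safety and tolerance of the three treatment arms". Section 5.4 lists as secondary endpoints the incidence of adverse events (7), of raised cholesterol and triglycerides (12) and of abnormal laboratory values (13).

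Time on the randomised drug need not be equal:
- Section 5.5.1 foresees interruption or change of study treatment for side effects or any other reason, and loss to follow-up.
- Section 6.1 adds, about the study as a whole: "The investigational site or the patient can anytime and of any reason decide to discontinue the study".
- Section 10 lets patients in arm 1, and only those, change the protease inhibitor for grade 3-4 hyperlipidaemia while staying on the visit schedule.

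The protocol does not say whether events after the randomised drug is stopped count in the chi-square.

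**The concern.** Two adjacent sentences treat time differently. For failure, the protocol chooses a method because it accounts for follow-up. For side effects, it fixes a yes/no comparison over up to three years. On-treatment, a patient who leaves the drug at week 8 has had one compulsory scheduled laboratory visit on it (week 4), while a patient who stays has eight (weeks 4, 12, 24, 48, 72, 96, 120 and 144). The chi-square gives both the same weight.

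If arms lose patients at different rates for reasons such as virological failure, preference or loss to follow-up, the on-treatment proportions mix the drug's side-effect rate with the time patients spent on it. Equal drugs could appear to differ, or a real excess in the arm with more stopping could be hidden. This matters most for late or cumulative effects, such as lipid and laboratory abnormalities.

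**Working it through.** **1. The plan's own figure.** Section 9 gives no figure for side effects. Its one calculation concerns treatment success: "N=65 in each one of two groups compared", and "if P1 is 0.70, e.g., then P2 has to exceed 0.90 for achieving the power 80"%. Exact power of the two-sided Fisher test at 65 per group with P1 = 0.70 is 0.775 at P2 = 0.90 and 0.803 at P2 = 0.905. The 80% line is crossed just above 0.90, so the statement reproduces. I take 65 per arm from it.

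**2. Inputs for the illustration.** Follow-up of 144 weeks and the 0.05 level are from section 9. The protocol gives no side-effect rate and no stopping rate by arm, so these are assumptions: 40% risk by week 144 at full exposure, a constant hazard, a fraction d stopping at week t for unrelated reasons, no stopping in the comparator, and events counted only on the randomised drug.

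**3. Size of the bias, equal true hazards.**
- Hazard h = -ln(0.6)/144 = 0.003547 per week.
- Risk up to a stop at week t: F(t) = 1 - exp(-h·t), so F(8) = 2.8%, F(24) = 8.2%, F(72) = 22.5%.
- Observed proportion = (1 - d)·0.40 + d·F(t).

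| d | stop at week 8 | week 24 | week 72 | comparator |
|---|---|---|---|---|
| 20% | 32.6% | 33.6% | 36.5% | 40% |
| 30% | 28.8% | 30.4% | 34.8% | 40% |

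For example, 0.7 × 0.40 + 0.3 × 0.028 = 0.288. With one of three arms affected and 65 per arm, the chi-square on 2 df rejects in 7% to 26% of trials across these six cases (noncentral chi-square), against a nominal 5%.

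**4. Stopping in every arm.** Let stopping be a constant hazard m, and measure time in units of 144 weeks. Then P(event seen) = l/(l + m)·(1 - exp(-(l + m))). Assume a 50% full-exposure risk in every arm (l = 0.693) and stopping of 20%, 20% and 50% by week 144 (m = 0.223, 0.223, 0.693). The observed proportions are 45.4%, 45.4% and 37.5%, and the chi-square rejects in 14.2% of trials. For full-exposure risks of 30% and 70%, rejection is 9.5% and 21.4%. With the same stopping pattern, a true hazard 1.28 to 1.39 times higher in the third arm (risks 30% to 70%) would show as equal presence.

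**5. When the bias shrinks or reverses.**
- Early onset: if the 50% risk falls wholly within the first 12 weeks, the arms with 20% and 50% stopping show 49.6% and 48.7%.
- Stopping caused by side effects: such a patient is already counted. If a share s of the stoppers stop for a side effect, the observed proportion is 0.7 × 0.40 + 0.3 × (s + (1 - s)·F(t)). At week 8, s = 0.5 gives 43.4% and s = 1 gives 58.0%, both above 40%. Break-even is s = (0.40 - F)/(1 - F): 38% at week 8, 35% at week 24 and 23% at week 72.
- Stopping in the comparator: with 15% also stopping at week 8 there, its proportion is 0.85 × 0.40 + 0.15 × 0.028 = 34.4%, so 28.8% against 40% becomes 28.8% against 34.4%.

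**The case against.** The strongest reply is that the direction is not fixed. A reader might infer that whichever arm more patients abandon will look safer. The documents do not support that. Section 5.5.1 expressly foresees stopping because of side effects; those patients count as having one, and past the break-even shares above the abandoned arm looks worse. This stands, and it limits the point to stopping for unrelated reasons.

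Second, the intention-to-treat count has equal planned follow-up in every arm, and roll-over patients stay on schedule. The early-stopping bias therefore belongs to the on-treatment analysis. The intention-to-treat count tends to err the other way, by adding later-regimen effects to the original arm. This stands too. The recorded relationship of each event to the antiretroviral agents (section 8) helps only in part.

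Third, toxicity-driven stopping is already covered: it is part of the survival-tested primary endpoint and of secondary endpoints 2 and 6. That is correct, but those endpoints measure stopping. They do not correct the comparison of side effects that did not lead to it.

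Fourth, crude incidence is a conventional safety summary, and exposure-adjusted rates or a counting window can be left to an analysis plan. That holds for the detail and for the missing window. The presence-only test, however, is written into section 9.

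Finally, one might infer that the trial expects the arms to differ in stopping. Sections 5.1 and 5.2 only ask whether they do.

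**Conclusion.** The point holds in a limited form. The presence-only chi-square takes no account of time on the randomised drug, and this can distort the on-treatment comparison of late or cumulative side effects and laboratory abnormalities. Under the stated assumptions the understatement is about 3 to 11 percentage points (36.5% down to 28.8% against 40%), with chi-square rejection of 7% to 26% where there is no true difference. These figures rest on an assumed risk, a constant hazard, no stopping in the comparator and stopping unrelated to side effects. Stopping in the comparator or early onset makes the distortion smaller, and stopping caused by side effects can reverse it. It does not follow that the whole safety assessment is biased towards the arm with most stopping. This is an inexpensive improvement to a secondary comparison and does not touch the primary analysis.

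**What to change.** For the on-treatment safety comparison, amend section 9 to:
- compare time to first side effect, and separately time to first laboratory abnormality, by a log-rank test stratified by the randomisation strata (CD4-cell count and HIV-1 RNA);
- count the event that triggers a stop, and censor at permanent stop of the randomised drug or week 144;
- report events per 100 person-years by arm;
- keep the crude proportions and the intention-to-treat chi-square alongside, saying whether events after the randomised drug is stopped are counted.

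No new data are needed: event onset dates are recorded under section 8 and treatment changes at each visit under section 7.2. The cost is analysis wording and programming.

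There are two downsides. Censoring at drug stop may be informative, so the result should be read together with secondary endpoints 2 and 6. Laboratory event times are known only to the interval between visits, which is 24 weeks from week 24 on.

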**2.3 Sample size**

Approximately 150-210 patients

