**5.5 Definitions for treatment and virological failure**

***5.5.1 Treatment failure***

Treatment failure is defined as:

1. Virological failure (see 5.5.2 for definition), or

2. Treatment interruption or change of study treatment due to side-effects (NRTI backbone are allowed to be changed, see 6.3), or

3. Treatment interruption or change of study treatment due to any other reason (NRTI backbone are allowed to be changed, see 6.3), or

4. Missed to follow-up

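### The 80% power statement is correct at 65 per arm, but the protocol permits 50 to 70 per arm, and below 65 the design does not deliver it

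*Protocol*

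**What the plan says.** The sample size appears three times, each time as a range:

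- Protocol 2.3: "Approximately 150-210 patients".
- Protocol 6.1: "An estimation of approximately 50-70 patients in each arm are to be included during two years".
- Protocol 9: "The trial will randomise (1:1:1) 150-210 subjects in three treatment arms".

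The power calculation, also in section 9, is for a single size: "N=65 in each one of two groups compared". One example is read from Figure 1, with P1 and P2 as the probabilities of treatment success: "if P1 is 0.70, e.g., then P2 has to exceed 0.90 for achieving the power 80" per cent. On the method, the section states: "The power calculation was performed for Fisher’s exact test at the level 0.05, two-tailed test, though survival tests will be used". It adds that a survival-test calculation would need specifications not yet available, and that the difference in power is small.

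No section gives power for another size, names 65 per arm (195 in total) as the target, or sets a minimum size.

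**The concern.** The sample size and its justification do not match. Three arms of 65 make 195 patients, whereas the range starts at 150, which is 50 per arm. That is 15 fewer per arm than the calculation assumes (15/65 = 23%). A trial that closes at 150 complies with the protocol, yet its power is stated nowhere.

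The primary objective is to find whether treatment failure differs between the three arms. If two arms truly differ by 20 points (0.70 against 0.90), the planning test misses this in about 36% of trials at 50 per arm (1 - 0.640), against about 22% at 65 (1 - 0.775). Anyone interpreting a non-significant result needs to know which of these applies.

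**Working it through.** **Inputs, all from the protocol.** P1 = 0.70; P2 at or just above 0.90; 65 per group; Fisher's exact test, two-tailed, level 0.05 (section 9); 50-70 per arm (section 6.1). No dropout inflation is stated. Loss to follow-up is itself a failure criterion ("Missed to follow-up", section 5.5.1), so such patients count in the endpoint.

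**Formula.** Exact power with n per arm:

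Power(n) = Σᵢ Σⱼ Bin(i; n, P1) · Bin(j; n, P2) · 1[Fisher two-sided p(i, j) ≤ 0.05], with i and j running from 0 to n.

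**Step 1: reproduce the protocol's figure at n = 65, P1 = 0.70.**

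| P2 | Power |
|---|---|
| 0.90 | 77.5% |
| 0.9045 | 80.0% |
| 0.905 | 80.3% |

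P2 does have to exceed 0.90 for 80% power. The statement is correct for 65 per arm.

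**Step 2: same test and level, 0.70 against exactly 0.90, over the permitted range.**

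| n per arm | Total | Power |
|---|---|---|
| 50 | 150 | 64.0% |
| 55 | 165 | 68.2% |
| 60 | 180 | 73.0% |
| 65 | 195 | 77.5% |
| 68 | 204 | just under 80.0% |
| 70 | 210 | 81.3% |

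**Step 3: compare like with like.** Take the P2 that gives 80% at 65 per arm, 0.9045. At 50 per arm the same difference has 66.7% power. So the fall from 65 to 50 per arm is from 80% to 67% at P2 = 0.9045, or from 77.5% to 64.0% at P2 = 0.90.

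**Step 4: P2 needed for 80% power when P1 = 0.70.** 0.928 at 50 per arm, 0.9045 at 65, 0.898 at 70.

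**Step 5: would the planned survival test close the gap?** The protocol gives no inputs for this, so proportional hazards and complete follow-up are assumed.

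- Hazard ratio = ln(0.90)/ln(0.70) = 0.295, so |ln HR| = 1.219.
- Expected events = n × (0.30 + 0.10): 20 at n = 50 and 26 at n = 65.
- Schoenfeld power = Φ(√(events/4) × |ln HR| − 1.96).
- n = 50: Φ(2.236 × 1.219 − 1.96) = Φ(0.77) = 77.8%.
- n = 65: Φ(2.550 × 1.219 − 1.96) = Φ(1.15) = 87.5%.

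Simulation of the log-rank test under exponential failure gives 72-73% at n = 50 and 83.5% at n = 65. With so few events the Schoenfeld approximation is rough. Both approaches give less than 80% at 50 per arm.

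**The case against.** The strongest reply is that nothing in section 9 is false. The calculation is openly tied to 65 per group, the 0.70/0.90 pair is offered as an example, and it reproduces. The protocol never claims 80% power at 150 patients. This stands: the arithmetic is right, and the defect is a mismatch between the basis of the calculation and the size that the protocol permits.

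Three stronger readings are tempting, and the protocol supports none of them.

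- *The statement holds at 65 per arm and nowhere else.* It also holds from 65 up to 70, where even exactly 0.90 gives 81.3%. The shortfall lies below 65.
- *Power drops from 80% to 64%.* This mixes two values of P2. The protocol says that P2 must exceed 0.90, and at exactly 0.90 power is already 77.5% at 65 per arm.
- *A 150-patient trial would be reported as having 80% power, and a null result taken as showing no difference.* Nothing in the text says so. The protocol makes no equivalence or non-inferiority claim, and a careful reader can see that the figure belongs to 65 per group.

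A further reply is that Fisher's test only stands in for the survival test. That partly stands: 64% is the power of the planning test, not of the primary analysis, and the survival test may have more. But the protocol gives no survival calculation, calls the difference small, and under the assumptions above the survival test still falls short of 80% at 50 per arm.

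One might also suppose that 65 is 70 less an allowance for dropout. The protocol does not say this, and it counts loss to follow-up as failure.

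Finally, the range is worded as approximate in 2.3 and 6.1. Section 9, however, says flatly that 150-210 will be randomised.

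**Conclusion.** The point holds as a mismatch, not as a calculation error. The only power statement is correct at 65 per arm, and the permitted size extends 15 per arm below that, to where the design no longer delivers it. By the protocol's own test and level, the loss at the lower limit is about 13 percentage points: 80% to 66.7% at P2 = 0.9045, or 77.5% to 64.0% at P2 = 0.90.

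The Fisher figures rest only on the protocol's stated inputs, for a single pair of arms at unadjusted 0.05, as in section 9. The 72-78% for the survival test at 50 per arm rests on assumed proportional hazards and is indicative only. Neither the analysis method nor the error rate is affected. What needs correcting is the stated justification for the lower part of the sample-size range.

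**What to change.** Either of two changes is enough.

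1. In section 9, restate the power for the permitted range, for example: *With P1 = 0.70, 80% power by Fisher's exact test (two-tailed, 0.05) requires P2 of about 0.93 with 50 per arm, 0.905 with 65 and 0.90 with 70.* At 65 per arm the figure should be given as 0.905 or as above 0.90, not as at least 0.90, because exactly 0.90 gives 77.5%.
2. Name 195 patients (65 per arm) as the planned size in sections 2.3, 6.1 and 9. This lies inside the existing range and matches the calculation already made.

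The first costs one sentence and makes the stated power less favourable at the lower end. The second keeps the present power statement but replaces a flexible range with a definite target, so that stopping at 150 would be a shortfall against plan.
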